# Aim, objectives and outcomes

This research asks: 1) Is it feasible to conduct a randomised trial within a cohort (TWiC) comparing OptiBreech Care for planned vaginal breech birth with external cephalic version, for women with a breech pregnancy at term?

The aim is to determine whether a TWiC is feasible and offers value for a future policy change.

## Objectives

**Cohort study:**

1. Pilot the OptiBreech cohort database using data from women participating in the OptiBreech 1 study, who have already given prospective consent for their data to be collected;
2. Measure the completeness of outcome data and time required to gather it;
3. Identify preliminary safety outcomes among a larger cohort of women planning a vaginal breech birth with OptiBreech Care, some of whom may not be eligible for randomisation.

**Trial delivery and design:**

1. Identify recruitment, adherence and retention rates to inform estimations for a full RCT;
2. Determine outcomes to be prioritised and sample size for a full RCT;
3. Determine with a Trial Steering Committee whether an RCT is feasible and offers value for a future policy change.

**Implementation evaluation:**

1. Assess the fidelity of the OptiBreech Care Pathway delivery within the cohort, based on the TiDIER checklist^58^;

**Economic evaluation:**

1. Identify the relevant resources and health services used and test appropriate methods for their measurement; and
2. Determine which costs and benefits to the NHS are feasible to measure in a full trial.

## Primary Outcomes

1. Recruitment rate recorded as the number of eligible participants who consent to participate in the study by 6 months (randomised) and overall (non-randomised);
2. Acceptance rate recorded as the number of participants randomised to OptiBreech Care who plan a vaginal breech birth, and the number of participants randomised to the control who attempt an ECV, measured at the time of birth;
3. Attrition rate recorded as the number of participants who consent to participate who remain in the study until the end of follow-up at 4 months after birth;
4. Long-term attrition rate recorded as the number of OptiBreech 1 participants who complete 1-year and 2-year follow-up surveys when invited;
5. Fidelity to intervention recorded as number of planned VBBs attended by a proficient team member, measured at the time of birth;
6. Costs to deliver the service recorded as total number of days and nights spent on call to support planned VBBs in the trial by 6 months.

## Secondary Outcomes

The following potential primary and secondary outcomes for a substantive trial will be feasibility-tested, and incidence rates will be used to inform power calculations for the substantive trial.

1. Admission to higher-level neonatal care, measured at 28 days following birth, as a binary (yes/no) and continuous (number of days/nights) outcome, from patients’ medical records;
2. Mode of birth measured using patient’s medical records on day of birth, as a categorial measurement to include the following categories: vaginal breech birth, forceps breech, pre-labour CS, emergency CS, cephalic vaginal birth, cephalic forceps, cephalic ventouse;
3. Composite neonatal perinatal death or serious adverse morbidity, measured at 28 days following birth, from patients’ medical notes; serious neonatal morbidity to include the following: 5 minute APGAR score <7, peripheral nerve injury present at discharge from hospital, skull fracture, spinal cord injury, admission to NICU>4 days, intubation/ventilation >24 hours, convulsions >24 hours, parenteral or tube feeding >24 hours;
4. Composite maternal death or serious morbidity, measured at 28 days following birth, from patients’ medical notes; serious maternal morbidity to include the following: postpartum haemorrhage >1000 mL, obstetric anal sphincter injury, cervical laceration involving lower uterine segment, vertical uterine incision or serious extension to transverse uterine incision, bladder, ureter or bowel injury requiring repair, dilation and curettage for bleeding or retained placental tissue, manual removal of placenta, uterine rupture, hysterectomy, vulval or perineal haematoma requiring evacuation, wound dehiscence / breakdown, wound infection requiring prolonged hospital stay / readmission / antibiotics, sepsis, disseminated intravascular coagulation;
5. Use of services following referral for breech care, to include antenatal and postnatal appointments, total time spent admitted to hospital, number of ECVs, number of ultrasound scans, and professionals present at birth, measured at 28 days following birth from patients’ medical notes;
6. Satisfaction with care, measured using previously validated survey questions with a 5-point Likert scale, at 1 month post birth
7. Experience of childbirth, measured using the ‘Childbirth Experience Questionnaire’^59,60^ at 1 month post birth
8. Health-related quality of life, using the PROMIS-10 survey^61^ at 1 month, 3-4 months, 1 year and 2 years following birth
9. Infant’s development, using the appropriate Ages and Stages Questionnaires at 3-4 months, 1 year and 2 years following birth^62^

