The OptiBreech 1 opened in January 2021, with 10 sites gradually joining the study throughout 2021 due to delays with R&D approvals affected by the COVID-19 pandemic (https://optibreech.uk/participating-sites/). This is a preliminary observational and qualitative feasibility study, aiming to determine whether there is a demand for vaginal breech birth, whether it is possible to implement the OptiBreech model of care, and how acceptable the OptiBreech model is to women and staff. As of 9 September 2021, a total of 27 women requesting a vaginal breech birth have been recruited to the study across 4 sites. A brief summary table is presented below, comparing our returned results so far, alongside the largest reported study of ECV outcomes in the UK.^40^

Table 2: Results of OptiBreech 1

*OptiBreech 1* – conducted in the hospitals participating in this randomisation study (to 7/9/21)

| **Outcome** | **OptiBreech 1**  *planned vaginal breech births following or without ECV attempt* | **Melo et al 2019 ECV study**  *gold standard UK ECV pathway* |
| --- | --- | --- |
| Total vaginal births | 48% (13/27) | 43.6% (1141/2614) |
| Spontaneous vaginal birth | 44% (12/27) | 33.1% (866/2614) |
| Instrumental birth  *(forceps or suction cup)* | 4% (1/27) | 10.5% (275/2614) |
| Pre-labour caesarean birth | 19% (5/27) | 36.6% (957/2614) |
| In-labour caesarean birth | 33% (9/27) | 18.5% (484/2614) |
| Baby turned head-down prior to labour following failed ECV | 4% (1/27) | 4% (57/1334) |
| Admission to NICU / SCBU* | 4% (1/27) | 3.6% (95/2614) |
| Stillbirth or neonatal death (within 28 days of birth) * | 0 | 0.19% (5/2614) |
| Someone present who had completed physiological breech birth training | 83% (10/12) | *Not reported* |
| Someone present who met all proficiency criteria | 75% (9/12) | *Not reported* |
| Less than 5 minutes elapsed between the birth of the pelvis and the birth of the head | 92% (11/12) | *Not reported* |
| Maternal birth position | Upright – 83% (10/12)  Supine (back) – 17% (2/12) | *Not reported* |

* The OptiBreech 1 study has not collected enough data to make a comparison on these outcomes, but we would expect results to be similar, based on the RCOG Guidance described below.

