**Cohort analysis**

Potential primary outcome = composite perinatal death or serious morbidity (maternal and neonatal) following enrolment

1. Groups 1: ECV (grey) versus planned VBB with no ECV (dark green). Cochrane review: Incidence of Apgar <7 at 5 minutes, 44/1000 following ECV, 70/1000 following no ECV, considered equivalent.
2. Groups 2: VBB with OptiBreech care (planned and unplanned) versus VBB without OptiBreech care (planned and unplanned) (all green, subgroups). In the Term Breech Trial,^45^ this rate was 5%. In the PREMODA cohort study,^71^ it was 1.6%.
3. Additional comparisons: all planned CS (all blue) vs all planned cephalic birth after ECV (yellow) vs VBB with OptiBreech care vs VBB without OptiBreech care (all green)
   1. Planned cephalic birth after ECV as control

Potential secondary outcome = mode of birth

1. Comparison: ECV attempted (grey) versus planned VBB with no ECV (dark green)
2. Comparison: VBB with OptiBreech team versus no OptiBreech team present (all green, subgroups)

We will report on incidence rates for all of these outcomes that may be used as comparators.

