# Definitions

Breech – ‘Breech’ refers to a breech-presenting fetus, that is lying in a longitudinal position, with buttocks, feet or knees closest to the cervical os.

CI – Chief Investigator. On behalf of the Sponsor, the CI has overall responsibility for the design and conduct of the study. The CI also has co-ordinating responsibility for reporting adverse events to the Sponsor and to the relevant Research Ethics Committee (REC).

CRF – Care Report Form. A paper or electronic questionnaire used to collect date on/from each participant.

CS – Caesarean section

R&D – Research and Development Office

GCP – Good Clinical Practice. Every clinician taking consent to participate in this research should have completed Good Clinical Practice training.

Independent Data Monitoring Committee (IDMC) – An independent data-monitoring committee that may be established by the sponsor to assess at intervals the progress of a clinical trial, the safety data, and the critical efficacy endpoints, and to recommend to the sponsor whether to continue, modify, or stop a trial.

OptiBreech Team – The care in this study is delivered by an ‘OptiBreech Team’, in which each member has undertaken physiological breech birth training and meets the OptiBreech Proficiency Criteria (p36).

PBB – Physiological breech birth. A physiological breech birth is a vaginal breech birth in which the woman is encouraged to remain upright and active throughout her labour and able to assume the position of her choice for the birth, including upright postures. Guidance for those attending PBBs is based on research on ‘physiological breech birth’ and includes recommended time limits around late second stage, and recommended interventions if these are exceeded. VBBs within the OptiBreech care pathway are managed according to PBB principles.

Perinatal death – A fetal death (stillbirth) or an early neonatal death (0-6 days). (Evaluation outcome definitions are taken from the MEASURE Evaluation Family Planning and Reproductive Health Indicators Database.^75^)

PI – Principle Investigator. Each site will have 1 PI, who should be either the Breech Lead Obstetrician or the Breech Lead Midwife. They will be responsible for overseeing the local data collection and for informing the CI of all SAEs that occur at the site. Along with the other Lead (Obstetrician or Midwife), they will also be responsible for clinically leading the delivery of the intervention.

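### Neonatal composite (secondary outcome 3): its death element stops at day 6 although it is measured at 28 days, and its Apgar <7 component is not reconciled with the 5% and 1.6% rates quoted for the composite

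*Protocol*

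**What the plan says.** Item 3 of the protocol's Secondary Outcomes is a "Composite neonatal perinatal death or serious adverse morbidity, measured at 28 days following birth, from patients’ medical notes". The morbidity list opens as follows: "serious neonatal morbidity to include the following: 5 minute APGAR score <7, peripheral nerve injury present at discharge from hospital". The introduction to that section says that "incidence rates will be used to inform power calculations for the substantive trial". Item 4 defines a separate maternal composite.

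The Definitions section gives "Perinatal death – A fetal death (stillbirth) or an early neonatal death (0-6 days"), and notes that evaluation outcome definitions come from an indicators database, so the entry is meant to govern outcomes. Table 2, in the section on feasibility testing so far, uses a different window: "Stillbirth or neonatal death (within 28 days of birth").

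Under Statistical analysis, the Cohort analysis part names a composite of perinatal death or serious morbidity as a potential primary outcome and labels it as both maternal and neonatal. For its first comparison it quotes "Incidence of Apgar <7 at 5 minutes, 44/1000 following ECV, 70/1000 following no ECV, considered equivalent". For its second it gives 5% from an earlier randomised trial of planned caesarean versus planned vaginal breech birth, then "In the PREMODA cohort study,^71^ it was 1.6" per cent. It promises to report incidence for the outcomes that may serve as comparators.

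**The concern.** There are two separate difficulties with one outcome.

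**Death window.** An outcome assessed at 28 days should count deaths up to that point. Under the protocol's own definition, a baby who dies on day 10 is counted as a death in Table 2 but not in item 3.

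**Apgar component.** In one population a composite cannot be rarer than any of its components. The rates quoted for 5-minute Apgar <7 alone mostly exceed the rates quoted for the whole composite. The Masking section itself names the Apgar score as a subjective judgement, made by staff who may know of an ECV attempt and of enrolment. The Neonatal Care part of Appendix 1 adds that breech babies often look depressed at birth and in most cases recover quickly. A staff-judged component that is often transient could therefore dominate a composite meant to describe serious morbidity.

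At stake are the safety description that goes to the steering committee and the baseline rate carried into planning a later trial.

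**Working it through.** The 5% and 1.6% are literature rates quoted without derivation, so there is no plan figure to reproduce. The sample size of 104 rests on precision of the recruitment rate, and the 2280 for a full trial rests on neonatal admission. Neither uses this composite.

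**1. Death window.**

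| Event | Death event in item 3 (Definitions) | Death event in Table 2 |
|---|---|---|
| Stillbirth | yes | yes |
| Death, days 0-6 | yes | yes |
| Death, days 7-27 | no | yes |

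Size: the protocol's one mortality figure with a 28-day window is Table 2's UK ECV cohort, 5/2614 = 0.19%. Deaths on days 7-27 are some part of that, hence a fraction of 0.2 percentage points if the cohort's rate carries over. In 104 women, all deaths in the window would number about 104 × 0.0019 = 0.2. The 0.5 to 2 per 1000 in Assessment of safety is labelled perinatal, so by the protocol's definition it omits days 7-27 and shows only the order of magnitude.

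**2. Component against composite.** Inputs from Cohort analysis: Apgar <7 at 4.4% (ECV) and 7.0% (no ECV); composite at 5% and 1.6%.

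| Apgar <7 | Composite rate | Ratio | Difference (points) |
|---|---|---|---|
| 4.4% | 5% | 0.88 | -0.6 |
| 7.0% | 5% | 1.40 | +2.0 |
| 4.4% | 1.6% | 2.75 | +2.8 |
| 7.0% | 1.6% | 4.38 | +5.4 |

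Three of the four pairs are impossible if definition and population are shared. The fourth is possible, but leaves only 0.6 points for every event without a low Apgar score.

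**3. Would a cut-off of <4 restore agreement?** Table 1 reports Apgar <4 in 4/69 = 5.8% of births with no trainee present (0/21 with one). That single component also exceeds both 5% and 1.6%, so the cut-off alone does not settle the matter.

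**4. Could population alone explain the gap?** The review behind the Apgar rates is quoted with neonatal admission of 121/1000 after ECV. Table 2's UK ECV cohort has 95/2614 = 3.6%, a ratio of 3.6/12.1 = 0.30. If Apgar <7 scaled in the same way (an assumption), 44 and 70 per 1000 become about 13 and 21 per 1000, on either side of 16 per 1000. So population could explain much of it.

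**5. Why the baseline matters for planning.** Illustration only, assuming the composite is halved, two-sided 5%, 80% power, 1:1 allocation and no dropout. Per arm, n = [1.96√(2p̄(1−p̄)) + 0.842√(p₁(1−p₁) + p₂(1−p₂))]² / (p₁−p₂)², with p₂ = p₁/2 and p̄ their mean.

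| Baseline p₁ | Total N |
|---|---|
| 1.6% | 5814 |
| 4.4% | 2068 |
| 5% | 1812 |
| 7.0% | 1274 |

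5814/1274 = 4.6, so the choice among the quoted rates moves the size of such a trial more than fourfold.

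**The case against.** The best defence is that no comparison with 5% or 1.6% is planned. The section lists what a future trial might use, its contrasts are between groups measured in the same way, and power would be based on incidence observed under the trial's own definition. The pilot is descriptive and is stated not to be powered for safety differences. The Apgar rates and the composite rates belong to different comparisons and different sources, and step 4 shows that population could explain the gap. Even the antecedent of the 5% is not spelled out; I take it to be the composite because that outcome heads the list. Apgar is collected as an ordinal value, so either cut-off can be derived later, and choosing outcomes for the full trial is itself an objective. On deaths, many babies dying on days 7-27 would enter the composite through a NICU stay over 4 days or ventilation over 24 hours, and every neonatal death is reported at once as a serious adverse event.

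Much of this stands. It removes any claim that a biased comparison is built into the pilot, and it makes replacement of the Apgar threshold a matter of preference. It does not remove the contradiction between a 28-day outcome and a day-6 death definition. Nor does it reconcile rates that the protocol sets side by side while promising to report incidences as possible comparators.

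**Conclusion.** The point holds in limited form. The death element of item 3 contradicts its own measurement time and Table 2. The effect is a fraction of 0.2 percentage points, taking the UK ECV cohort's 28-day rate as a guide. Separately, Apgar <7 is quoted at 0.88 to 1.40 times the 5% rate and 2.75 to 4.38 times the 1.6% rate, so the pilot's incidence cannot be interpreted against either without their definitions. The label adds to this: the quoted rates are attached to a maternal and neonatal composite, whereas Secondary Outcomes defines two separate ones.

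Three stronger readings are tempting and are not supported:

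- A reader might infer that the studies behind 5% and 1.6% used a stricter Apgar threshold. The protocol gives neither their thresholds nor their components.
- A reader might add the Apgar rates to 1.6% (1.6 + 4.4 = 6.0%; 1.6 + 7.0 = 8.6%) and conclude that OptiBreech care will look 4 to 7 points worse by definition alone. That needs the Apgar rates to carry over, no overlap between components, and a 1.6% that excludes Apgar <7. None of these is established.
- A reader might infer that <7 must be replaced by <4. Step 3 shows that this would not by itself make the rates comparable.

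The consequences are for the safety description and for planning a later trial. The pilot's primary outcomes and its sample size are unaffected.

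**What to change.** 1. In item 3, replace perinatal death by *stillbirth or neonatal death within 28 days of birth*. The Definitions entry can stay for the perinatal mortality rate.
2. Keep the composite with 5-minute Apgar <7, report it also with Apgar <4, and report Apgar <7 on its own.
3. In Cohort analysis, say whether the neonatal composite, the maternal composite or a union of the two is meant. Do not set the observed composite against 5% or 1.6%, or use those rates for power, until their component definitions are stated and matched to item 3.

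The cost is wording and a few extra table rows. The case report form already holds the 5-minute Apgar score as an ordinal value and death status with its date, and data are due within 6 weeks of birth, which covers the 28 days. The version with Apgar <4 will have fewer events, which matters little in a descriptive pilot.

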# Study design and Flowchart

This study uses a Trial Within Cohort (TWiC) design. That is, some of the women contributing their data will be randomised and others will not be.

## The OptiBreech Multiple trial cohort (OptiBreech mTC)

This study will establish and use a cohort database for a long-term prospective observational study of OptiBreech care. That is: care for breech presentation at term based on the principles of physiological breech birth and delivered by specialists with a specified minimum level of training and proficiency. Once refined, the intention is that multiple centres delivering this type of care will be able to contribute data in order to establish more robust and generalisable measurements for safety outcomes. A majority of studies of care for breech presentation at term are small, single-centre observational studies, which often do not involved numbers large enough to evaluate the questions that are most important to service users, such as the current perinatal mortality, serious morbidity and long-term impairment. Collecting observational cohort data, among women who decline or are ineligible for randomisation, or within sites that are not yet participating in the randomisation element, will enable the results of the randomised study to be contextualised.

The OptiBreech database will be piloted by collecting the full data set from the medical notes of women who participated in OptiBreech 1. These women have already given consent for their data to be used and identifiable information to be retained for future research. We will pilot the case report form (CRF) and the on-line database by retrospectively collecting their data and entering it into the database. They will be an internal pilot, included in the non-randomised cohort group. Refinements will be made to the CRF and/or database to improve the quality of the dataset we are able to obtain for the OptiBreech mTC.

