Although it is too early to conclude anything from these results, a few observations can be made. Firstly, where a genuine specialist midwife is in operation and attending most/all of the vaginal breech births, as is/was the case in two of the sites, there appears to be a significant demand for this service. These two Trusts, comprising a total of three hospitals, have been responsible for 21/27 of the women recruited in the OptiBreech 1 study. They are the only two sites to meet the inclusion criteria for OptiBreech Care. There has been 100% proficient attendance at these sites and no neonatal admissions.

In contrast, attempts to set up a multi-disciplinary team at other sites have been largely unsuccessful or are progressing slowly. This may be because the implementation approach used is not adequate/feasible or because the demands of dealing with the pandemic have hampered the ability to develop specialist skills within a service where they are not already operational. For example, several sites have indicated face-to-face training is needed, but this has been very challenging to arrange due to social distancing measures in place and persistent staff shortages. All adverse outcomes and lack of attendance of proficient OptiBreech team members have been in sites not currently included in this randomisation pilot. We will continue to observe what is happening in these sites to gain insight over a longer period of time, but no site will be able to randomise women in this study until the site eligibility criteria have been met.

Finally, our team has completed a review of outcomes associated with effectiveness studies of breech birth at term.^54^ This included significant involvement of our PPI group, to ensure that women’s voices influenced our choice of outcome data points. The influence they have had on our work is described in the publication.

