# Participant Selection

## Sites

All NHS sites who are providing OptiBreech Care are eligible to contribute data to the cohort study.

Site requirements for participation in the pilot randomisation include:

1. Recruited a minimum of 5 women to OptiBreech 1 or the non-randomised cohort of OptiBreech mTC
2. Achieved at least 90% fidelity to the intervention (attendance of someone with training and/or proficiency, <5 minutes from pelvis to head and use of maternal movement and effort prior to hands-on assistance) for a minimum of 5 vaginal breech births
3. Able to present a plan for recruitment and randomisation for a minimum of 2 women per month who provide fully informed consent to taking part in the study, immediately following diagnosis of breech presentation by USS, prior to counselling for ECV/mode of birth
4. Able to ensure a member of the OptiBreech team is available to provide counselling for women randomised to ‘offer OptiBreech Care’
5. Able to include the Physiological Breech Birth Algorithm in annual mandatory training activities for all staff. This should cover: The recommended 7-5-3 minute time limit guidance; actions in response to delay in second stage, including delay on the perineum; physiological neonatal transition, including initiation of resuscitation where required with umbilical cord intact; effective communication; and maintaining a helicopter view
6. Identification of a Breech Specialist Midwife and/or Obstetrician with dedicated time to co-ordinate OptiBreech care and training, ability to deliver the physiological breech birth training package and commitment to participate in on-going professional development seminars provided by the research team throughout this trial.

Sites will be able to demonstrate adherence to these criteria during their participation in the OptiBreech 1 study.

We will initially include 2 Trusts, including 3 hospital sites, in the randomisation pilot. Approximately 4% of women have a breech pregnancy at term, and we can expect at least half of these to be eligible for randomisation. Feasibility testing as part of OptiBreech 1 indicated that we can anticipate half of these again, or 1% of all women, will consent to randomisation in this study. Sites will be expected to recruit a minimum of 10 participants willing to be randomised over a 6 month period.

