In order to proceed with a vaginal breech delivery as part of the OptiBreech trial, it is mandatory for one fully proficient OptiBreech Team member to be present throughout the active second stage (i.e. from starting pushing, to completion of delivery), to offer support and maintain situational awareness. Hands-on clinical care should be provided by someone who has received physiological breech birth training as described above, either through completion of the OptiBreech training package or as part of annual mandatory training activities. If this level of training and experience is not available, the situation must be escalated to the on-call consultant to decide whether to discuss with the woman, whether a standard vaginal breech delivery can be considered or alternatively, whether delivery by caesarean section is required.

Ability to have a proficient team member attend 90% of planned vaginal breech births is a criterion for entering the randomisation component of this study. This will be confirmed either through participation in OptiBreech 1 or through enrolment of women requesting a VBB in the observational cohort study.

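### The fidelity outcome mixes births before and after site opening, so it cannot show delivery once randomisation is running, and it reads high for randomising sites

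*Protocol*

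**What the plan says.** **Entry rule.** Protocol section Sites sets two conditions that matter here. The first is "Recruited a minimum of 5 women to OptiBreech 1 or the non-randomised cohort of OptiBreech mTC". The second is "Achieved at least 90% fidelity to the intervention" over at least five vaginal breech births. Section Proficiency criteria restates the second condition as a proficient member attending 90% of planned vaginal breech births (VBBs), and adds: "This will be confirmed either through participation in OptiBreech 1 or through enrolment of women requesting a VBB in the observational cohort study".

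**Cohort membership.** The section on the OptiBreech Multiple trial cohort has OptiBreech 1 records entered retrospectively in the new database and says of these women: "They will be an internal pilot, included in the non-randomised cohort group". Births of cohort women used to qualify a site are in the cohort already. Section Sites also opens the cohort to every NHS site giving OptiBreech care, whether or not it qualifies to randomise.

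**Reporting.** The implementation objective is "Assess the fidelity of the OptiBreech Care Pathway delivery within the cohort". Primary outcome 5 is "Fidelity to intervention recorded as number of planned VBBs attended by a proficient team member", measured at the time of birth. Section Statistical analysis repeats it and names the mTC database as the source. No section separates births that qualified a site from births that followed.

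**Results already known.** In section Feasibility Testing, Table 2 gives 9 of 12 births with a fully proficient person present, over all OptiBreech 1 sites. Of the two Trusts ready to randomise it says: "There has been 100% proficient attendance at these sites and no neonatal admissions". It places every lapse in attendance and every adverse outcome at sites not in the randomisation pilot.

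**The concern.** The Trial Steering Committee (TSC) needs to know whether sites deliver the intervention while they are randomising. A site's qualifying births cannot tell it that, because the site was admitted on the condition that those births went well. Counted together with later births, they raise the site's figure and dilute any fall after opening.

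This matters because section Protocol compliance promises the TSC a fidelity report at the end of the randomisation pilot, and serious non-compliance may stop recruitment at a site. Fidelity does not enter the Green/Amber/Red formula, so that report is where a fall would be seen.

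For safety the point is smaller. Results already in hand, extracted retrospectively, are mixed with those of women enrolled prospectively.

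**Working it through.** **The plan's own figure.** Table 2: 9/12 = 75.0%, reproduced (exact 95% interval 43% to 95%).

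**Inputs**
- Entry threshold 90%, minimum 5 births (section Sites).
- Number of randomising sites: 2 Trusts or 3 hospitals at the start (section Sites); 5 sites in section Sample size calculation and in the Green/Amber/Red example.
- Later planned VBBs: 52 − 30 = 22, the women who accept OptiBreech care in the Green/Amber/Red example. This only sets a scale.
- True fidelity after opening: not known. 75% and 90% are assumed.

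**Step 1: what the rule admits.** With 5 births, 4/5 = 80% fails, so a pass at the minimum means 5/5. If births are independent with true fidelity p, the chance of passing is p^5: 0.75^5 = 0.237 and 0.90^5 = 0.590. A site at 75% passes about one time in four, and its qualifying births then read 100%.

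**Step 2: randomising sites, run-in pooled with later births.** For s sites, pooled fidelity = (5s + 22p)/(5s + 22).

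| Sites | True 75% | True 90% |
|---|---|---|
| 2 | 26.5/32 = 82.8% | 29.8/32 = 93.1% |
| 3 | 31.5/37 = 85.1% | 34.8/37 = 94.1% |
| 5 | 41.5/47 = 88.3% | 44.8/47 = 95.3% |

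The excess is about 8 to 13 percentage points at a true 75%, and 3 to 5 points at a true 90%. It shrinks as later births accumulate: with 52 later births a true 75% reads 79.0%, 80.6% and 83.1%.

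Five proficiently attended run-in births per site is the minimum under the rule as restated in section Proficiency criteria, not a count from Table 2. That table has only 9 such births over all sites. Taking all 9 as the randomising sites' run-in, the most it could be at that date, a true 75% reads (9 + 16.5)/31 = 82.3% and a true 90% reads (9 + 19.8)/31 = 92.9%.

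**Step 3: all cohort sites.** Births at sites that did not qualify are also in the cohort. Adding all 12 OptiBreech 1 births to 22 later births at 90% gives (9 + 19.8)/34 = 84.7%, below the later rate.

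**Step 4: simulation.** Ten sites, true fidelity 75%, 5 run-in births each, 100,000 replicates:
- all sites pooled: 0.75;
- admitted sites, run-in only: 1.00;
- admitted sites, run-in plus 5 later births: 0.875;
- admitted sites, later births only: 0.75.

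Only a figure for randomising sites that includes the run-in is inflated by selection. Leaving the run-in out restores the true rate.

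**The case against.** The best case against the point has four parts.

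1. **Outcome 5 may not include OptiBreech 1.** Primary outcome 4 names OptiBreech 1 participants and outcome 5 does not. Outcome 5 is measured at the time of birth, whereas OptiBreech 1 data are entered later. Which records enter which table is often left to the SAP, which is not at hand. This leaves room for another reading. But the protocol itself puts these women in the cohort, sets fidelity as an objective within the cohort, and reports from that database. Cohort births used to qualify a site would remain in any case.

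2. **The measures differ.** Section Sites accepts training and/or proficiency, adds two technique items and counts vaginal breech births; outcome 5 counts proficient attendance at planned VBBs. This is correct for that section, but section Proficiency criteria states the rule on the same measure as outcome 5. The overlap is real, though not complete.

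3. **The TSC sees OptiBreech 1 separately.** Section Meeting schedule has it review those data before randomisation starts. This helps, but does not keep the same births out of the later figure.

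4. **No fall after opening is documented.** True. The 75% is the all-site OptiBreech 1 figure, while the Trusts ready to randomise stood at 100%. The calculation shows what pooling would hide, not what is expected.

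A reader might go further and infer that the entry rule fixes the cohort's fidelity and safety results. The documents do not support that. Non-qualifying sites contribute births, so the cohort-wide figure is not truncated. None of the six site criteria is a safety outcome, and the one OptiBreech 1 neonatal admission and the adverse outcomes elsewhere also enter the cohort.

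**Conclusion.** The point holds in a limited form. Primary outcome 5, as the protocol sets it, combines delivery before and after site opening. For randomising sites the combination is biased upwards: a true 75% would read about 83% to 88%. Across all cohort sites it is not inflated by the rule and may be pulled down, to 84.7% in the example with a later rate of 90%. In neither case does it show whether sites deliver the intervention once randomisation is running.

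The sizes assume independent births, the 5-birth minimum at each site and 22 later births; the protocol gives no run-in counts by site. For safety, the point is only that known, retrospectively collected results are mixed with prospective ones. The randomised comparison is untouched, because run-in women are not randomised, and the Green/Amber/Red formula has no fidelity term. This is a reporting defect that should be put right before the TSC's final review. It does not undermine the pilot.

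**What to change.** Add wording to two sections of the protocol, the OptiBreech Multiple trial cohort and Statistical analysis, to state that:

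- for randomising sites, primary outcome 5 is computed on planned VBBs enrolled after the site opened to randomisation, with numerator and denominator shown;
- OptiBreech 1 births, and any cohort births used to qualify a site, are tabulated separately as run-in and kept out of any randomising-site fidelity figure sent to the TSC;
- cohort safety outcomes are shown separately for OptiBreech 1 women and newly enrolled women.

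OptiBreech 1 data still serve to pilot the case report form and database, and no data are lost. The cost is smaller denominators, hence wider intervals, and possibly a less favourable fidelity figure.
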